**Figure 2: Definition of CMC who are MFTD**

[figure not shown]

### 3.3 Interventions

Patients will be randomized to receive either *usual care* for 1 year prior to their first clinic appointment (wait list group) or enrolled to be seen as soon as possible in a *complex care clinic* as part of the CCKO initiative. All eligible patients will be randomly assigned to wait list or the clinic prior to being approached for consent to participate in the evaluation of CCKO. The CCKO intervention involves intensive care coordination, defined as: “deliberate organization of patient care activities between two or more participants (including the patient) involved in a patient's care to facilitate the appropriate delivery of health care services. Organizing care involves the marshaling of personnel and other resources needed to carry out all required patient care activities and is often managed by the exchange of information among participants responsible for different aspects of care” (24). Within CCKO, intensive care coordination will specifically include: 1) the tailored, family/health care provider co-creation and regular updating of care coordination plans for each child which will be 2) facilitated and accounted for by key

workers partnering with families. The key worker would have a nursing or nurse practitioner background and will support providers in enacting the coordinated care plan between acute care, primary care, rehabilitation, home and community care. The key worker would be available to provide advice from Monday to Friday, 9 AM – 5 PM, and will also develop plans of care for emergencies after hours as part of care plan development. Resources to maintain intervention fidelity among key workers will be created and checked with oversight by PCMCH and the workers will connect annually in a meeting that will be co-attended by family representatives.

The wait list group consists of CMC who are receiving various types and levels of care from primary and specialty care providers, and are waitlisted for complex care clinic (pre-enrolment control period). Standard of care during the control period will involve care delivered through a primary care provider (family physician or paediatrician), with subspecialty consultation as needed. This is the model of care for the vast majority of CMC in Ontario; among ~6,200 CMC in Ontario, only ~500 receive care in a structured complex care clinic. At the end of 1 year, all CMC randomized to the wait list group will be offered enrolment in the complex care clinic and data will continue to be collected for 1 additional year on all participants in an extension phase.

### 3.4 Outcomes

In partnership with health care providers and CMC families, a Family-Engagement Evaluation was conducted to identify patient-centered criteria for determining effectiveness of the intervention. The core set of relevant PROMs and PREMs was created in a consensus meeting using data collected from an online survey completed by 48 families of children aged 2-21 years from all five CCKO regions, as well as 86 health care providers. This core set informed the development of a framework for CMC as summarized in **Figure 3**.

**Figure 3 – The CMC Family-Engagement Evaluation Framework**

[figure not shown]

Measures representing these outcomes are selected based on their content applicability to the outcomes, proven psychometric performance (reliability and validity) among children and families with chronic health conditions, and the option for child report wherever possible. The family-Engagement Evaluation

includes general and specific outcomes within the domains of service delivery (primary and secondary outcomes); child outcomes (secondary) and parent outcomes (secondary). Feeding and swallowing performance, as well as satisfaction with medical devices and assistive technology, were identified as priorities for the evaluation by patients and clinicians, however these PROMs could not be found in the literature. As part of the Family-Engagement Evaluation, a team of complex care healthcare providers and measurement specialists will be working on developing appropriate measures for these core outcomes. However for the purpose of this study, only outcomes for which there are validated tools will be measured.

An overview of the included outcomes and their measures are presented in **Figure 4**. Selected outcomes will be assessed at enrolment (t=0), 6 months, 12 months, and 24 months post-randomization so that all subjects will be asked to provide two full years of data. A demographics survey will also be administered during enrolment to capture descriptive, background information of the two groups at baseline. Demographics information includes: sex, age, ethnic background, marital status, education level, and employment status. Qualitative interviews will be conducted at the end of the intervention with a subsample (n = 25) of families in order to capture their overall experience with the intervention, areas of improvement, barriers and/or challenges associated with the intervention, as well as perceived benefits.

**Figure 4 – Overview of Outcomes and Associated Measures**

| Service Delivery Outcomes (Measurement Tool)       | Parent Outcomes (Measurement Tool)  | Child Outcomes (Measurement Tool)   | Health System Outcomes (Measurement Tool)                              | Process Outcomes (Measurement Tool)                                                                                                  |
|----------------------------------------------------|-------------------------------------|-------------------------------------|------------------------------------------------------------------------|--------------------------------------------------------------------------------------------------------------------------------------|
| Coordination Among Providers (FECC^)               | Life Satisfaction (KIDSCREEN, SWLS) | Life Satisfaction (KIDSCREEN)       | Health Utilization (ICES)
e.g. Hospital admissions, ER visits, etc. | Patient and family experience (Qualitative Interviews)
e.g. Overall experience with intervention, barriers and facilitators, etc. |
| Coordination Between Providers and Families (FECC) | Overall Health (PROMIS)             | Physical Pain (VAS)                 |                                                                        |                                                                                                                                      |
| Utility of Planning/Follow-Up Tools (FECC)         | Energy and Fatigue (PROMIS)         | *Feeding and Swallowing Performance |                                                                        |                                                                                                                                      |
| Individual family experiences with                 | Out of Pocket Expenses (Expense     | *Satisfaction with Medical and      |                                                                        |                                                                                                                                      |

|                                        |        |                   |  |  |
|----------------------------------------|--------|-------------------|--|--|
| care coordination
indicators (FECC) | Diary) | Assistive Devices |  |  |
|                                        |        |                   |  |  |

\*Outcome measures to be developed as part of the Family-Engagement Evaluation; ^Primary outcome measure

**Service Delivery (Primary) Outcomes:** The service delivery outcomes identified as the most important from the consensus project were:

1. *Coordination of Care Among Health Providers and Families*
2. *Coordination of Care Between Health Providers and Families*
3. *Utility of Follow-Up Planning Tools*

These outcomes will be assessed with the Family Experiences with Coordination of Care (FECC) survey, as the primary outcomes measure for this study. The FECC has been validated on 1209 US CMC patient-families, and has been reported to have internal consistency >0.7 with proven discriminant validity for patient-family socioeconomic status and rurality (25), as well as responsiveness to change demonstrated in a recent CMC randomized control trial (RCT) (26). In the US sample on which it was validated, the FECC is composed of 20 separate indicators. Indicators within the FECC that map onto the family-provider prioritized outcomes from Ontario (Coordination of Care Among Providers and Families (FECC-8a, 8b); Coordination of Care Between Providers and Families (FECC-5); and, Care Planning Tools (FECC-16, 17) will be used to assess the primary study outcome.

3 of the 20 indicators will not be collected (FECC-15, 19, and 20) as they have content relating to: electronic-health records (FECC-19 and 20), which are not universally available in the region of the CCKO intervention; and translation services (FECC-15), which are less relevant in a study population limited to English-speakers. Individual FECC indicators will be assessed as secondary outcomes.

**Child (Secondary) Outcomes:** The child-specific outcomes that will be measured are:

4. *Quality of Life and Overall Emotional Health*
5. *Child's Physical Pain*

Children's quality of life and emotional wellbeing will be measured using the World Health Organization definition focused on subjective life appraisal (27) and a positive orientation of mood assessment respectively. These outcomes will be assessed using the using the "Feelings" subscale from the KIDSCREEN-52 (6 items), used in over 250 studies in the child health services literature since its publication in 2005 (28, 29); and represents the most suitable content overlap with CMC children.

Children's physical pain will be measured using only self or proxy reports of pain according to a 10 cm linear Visual Analog Scale (VAS) (30). Linear VAS is considered to superior to other pain reports available for children due to consistencies of interpretation within parent-child dyads, test-retest reliability and measurement precision (31), and is most appropriate for the diverse functional ability of the CMC population.

**Parent (Secondary) Outcomes:** The parent outcomes identified as the most important from the consensus project were:

6. *Parents' Quality of Life*
7. *Perceived Emotional and Physical Health*
8. *Energy and Fatigue*
9. *Effects of Child's Condition on Parents' Finances and Ability to Work*

Parents' quality of life will be measured according to a subjective life appraisal definition with two scales.

The first will be Diener's highly validated Satisfaction with Life Scale (SWLS) (5 items) which is the most validated life satisfaction scale in health and social sciences literature (32, 33). The second is an adapted version of the KIDSCREEN survey subscale for Feelings (28,29).

Parents' perceived health, energy, and fatigue will be assessed with short forms of the Patient Reported Outcomes Measurement Information System (PROMIS) General Health (10 items); Sleep (8 items); and Fatigue (8 items) scales. These scales have been validated, have norm references data for comparison and have shown good to excellent psychometric properties among caregivers (34, 35).

Financial Impact on Parents' will be measured using an Expense Diary survey created by the co-investigators. This survey will capture financial impact based on lost time and ability to work, as well as out of pocket expenses for health care services, equipment, and travel using scales customized for CMC and standardized relative to various child health studies with the support of OCHSU investigators.

#### **Health System Outcomes:**

A cost-comparison will be presented as part of the trial findings. A cost-effectiveness analysis will be performed alongside this clinical trial to estimate the incremental costs (or savings) of the CCKO intervention compared to standard care in reducing hospitalizations. Both a health care system and societal perspective will be used with a time horizon of 12 months. Cost-effectiveness will be expressed as an incremental cost-effectiveness ratio (ICER) for each of the health care system and societal perspectives, expressed as point estimates and 95% confidence intervals. Given potential challenges in caregiver recall of out-of-pocket expenses and the lack of robust data on loss of productivity, the health care system perspective will be the primary health economic analysis.

**Process Outcomes:** Exit interviews with parents of children who received the intervention will be performed with the goals of: i) assessing the active ingredients of the intervention; ii) determining the fidelity of the intervention, iii) the 'dose' of intervention received, and iv) the elements of context that facilitate or hinder the intervention. All of these objectives will be probed with the purpose of learning the patient perspective of the intervention. Interviews as opposed to focus groups were chosen to encourage the unique experiences of each patient-family to come forward.

*Detecting Response Shift:* Parents and children affected by medical complexity have been shown to undergo a chronic disease adaptation process over time (36, 37). This can be a negative or positive shift in their expectations or priorities, which also effects their scoring of health and quality of life components. For example, if a parent expects a disease cure at baseline but shifts to an expectation that their child's

disease is managed to minimize morbidity after 12 months; a positive response shift has occurred. This is an adaptive phenomenon from a clinical perspective but can result in falsely concluding there was an improvement where there was none (Type I error). The error manifests an improvement in the response option scoring because the parent's calibration of poor to excellent on a Likert type scale shifted during the trial.

The opposite, negative response shift can also occur; the threshold for satisfaction with service provision can increase as a parent becomes more experienced. This can result in a negative change score even where there were authentic gains due to the intervention (Type II error). Mitigating this phenomenon called 'response shift' has a simple but rigorous solution called a 'then test' (38), which will be instituted for exploratory analyses. The then test will be implemented for the child (via the KIDSCREEN survey) and parent quality of life measures (using PROMIS tools) at 6, 12, 18 and 24 months for both intervention and waitlisted groups.

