### **Primary Research Question:**

1. a) What is the comparative effectiveness of the CCKO intervention relative to the waitlisted group?
- b) What are the elements that explain the successes and gaps of the intervention?

**Hypothesis:** We hypothesize CCKO will lead to improved variety of patient- and family-centred outcomes, while decreasing unnecessary healthcare utilization. In particular, we hypothesize that the intervention will:

- i) Improve coordination among health care providers and families;
- ii) Improve children's and parents' quality of life by decreasing the amount of time and effort spent on coordination of care;
- iii) Decrease parental fatigue;
- iv) Improve families' experiences with their child's health care;
- v) Decrease utilization of health services outside the immediate scope of care (i.e., hospital admissions, ER) as a result of improved coordination.

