#### Exclusion Criteria:

- a) High Utilization of hospital level care
  - $\geq 3$  hospitalizations,  $\geq 2$  ICU admissions,  $\geq 30$  days of total hospitalization in previous 3 months, excluding newborn admission
- b) Patient with tracheostomy and home ventilation
- c) Medical Status is deemed highly fragile and the need for close follow-up is deemed essential by both referring and triaging team
- d) Already followed by a complex care team
- e)  $>16.0$  years of age
- f) Inadequate English language skills to comprehend study questionnaires
- g) Parent will not be involved in child's care over entirety of study period (2 years)

Patients whose caregivers cannot complete questionnaires in English will not be involved in the primary analysis which involves patient-reported outcome measures (PROMs) and patient-reported experience measures (PREMs) that are written and validated in English, but in order to ensure equitable access to this novel service, they will be allowed to enrol in the clinic and if possible provide health care utilization data via health card linkages at ICES that will be used in secondary analyses. Similarly, we will exclude those patients who are thought to be in need of urgent care coordination by their clinicians (e.g. acuity deemed urgent for care coordination due to new technology such a tracheostomy/ventilation or significant medical complexity with an prolonged inpatient stay), but these patients will contribute data with consent through linkage through their health card to routinely available health administrative data.

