- vi) Health System Outcomes: A cost comparison analysis will be performed as part of the primary analysis. Additionally, cost-effectiveness will be subsequently performed, expressed as an incremental cost-effectiveness ratio (ICER), calculated by dividing the incremental costs of the intervention by the incremental difference in hospitalization days during the study period as the primary analysis and an ICER denominated on emergency department visits as a secondary analysis. Direct health care costs will include cost of the CCKO intervention and health services use by participants during the 12 month follow up period. Health services use by participants and covered by the provincial payer will be obtained through administrative data from the linkage with ICES. This will be expressed as absolute difference between the two groups with a 95% confidence interval. An interview administered expense diary will capture indirect costs, parent out-of-pocket expenses and additional health services covered by third-party payers. Intervention costs will include all Health Human Resources required to execute the intervention and will be allocated evenly across all participants. Extensive sensitivity analysis will be used to test the robustness of the results and explore uncertainty in any of the underlying assumptions. Probabilistic sensitivity analyses (PSAs) will also be used to establish the point estimate and 95% confidence interval for the ICERs obtained. The time horizon for the primary analysis will be one year, bounded by the date of randomization and the one year follow up interview.

Additional Analyses:

- i) All analyses will be extended to 24 months to assess for any outcomes that may have delays in change and to assess for ongoing effects in enrolled subjects. All primary and secondary analyses will be conducted for Year 2 of the study comparing outcomes among patients in the two groups that they were assigned to.
- ii) Comparison of PROMs and Interview Data: Qualitative interview data will be compared with PROMs to ascertain the association between experience-related themes and specific health outcome measures. Data on PROMs will be stratified based on scores for different outcomes, and compared with the qualitative data to gain a better understanding of how families' experiences with the intervention mapped on to patients' health-related outcomes.

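### The cost-effectiveness ratio is to carry a 95% confidence interval although its denominator, the difference in hospital days, may not be clearly different from zero; the interval may then not be interpretable

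*Protocol*

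**What the plan says.** Section 3.4 (Health System Outcomes) plans an economic analysis to "estimate the incremental costs (or savings) of the CCKO intervention compared to standard care in reducing hospitalizations". The result is an ICER for each of two perspectives, health care system and societal, "expressed as point estimates and 95% confidence intervals".

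Section 3.12, item vi, defines the primary ICER as the result of "dividing the incremental costs of the intervention by the incremental difference in hospitalization days" and adds "an ICER denominated on emergency department visits as a secondary analysis". It names the source of the interval: "Probabilistic sensitivity analyses (PSAs) will also be used to establish the point estimate and 95% confidence interval for the ICERs obtained". On follow-up it states: "The time horizon for the primary analysis will be one year".

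The same item also plans a cost comparison and an absolute between-group difference with a 95% confidence interval. The protocol mentions no cost-effectiveness plane, acceptability curve or net-benefit measure, and has no rule for a denominator near zero or of the unexpected sign.

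**The concern.** A ratio has a well-behaved confidence interval only if its denominator is clearly away from zero. Three features of this trial make that doubtful for hospital days.

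- Section 3.6 sizes the trial on a standardised effect of 0.5 SD, justified by a developer's recommendation for a measurement scale. Hospital days play no part in it.
- The hypotheses in section 2.2 give a direction for service use ("Decrease utilization of health services outside the immediate scope of care") but no size.
- Section 3.2 excludes children with "High Utilization of hospital level care", and the horizon is 12 months. Both may limit the difference in days that can be achieved.

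The numerator is not fixed in sign either, since section 3.4 foresees costs or savings. A negative ratio can then mean cheaper with fewer days, or dearer with more days. These are opposite conclusions for a payer, and one interval ordered from low to high cannot separate them. At stake is whether the pre-specified statement of uncertainty about value for money can be read.

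**Working it through.** **Inputs from the protocol.** Section 3.6: two-sided 5% level, 80% power, 0.5 SD, 10% loss, 140 in total (70 per arm). Section 3.8: 1:1 allocation. Sections 3.4 and 3.12 vi: the ICER definition and its interval.

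**Inputs that are assumed.** The protocol gives no SD, mean or expected difference for hospital days. The true difference is therefore expressed in SD units, d, and varied from 0 to 0.5. A normal approximation is used for the difference in means.

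**Step 1: reproduce the sample size.**

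n per arm = 2 × (1.96 + 0.842)² / 0.5² = 62.8, rounded up to 63. Allowing for 10% loss, 63 / 0.9 = 70 per arm, 140 in total. This matches the protocol, so the size follows from a 0.5 SD effect alone.

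**Step 2: precision of the denominator.**

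In SD units, SE = √(2/n).

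- 70 per arm: SE = √(2/70) = 0.169. The expected z reaches 1.96 at d = 1.96 × 0.169 = 0.33.
- 63 per arm: SE = √(2/63) = 0.178. The threshold is d = 1.96 × 0.178 = 0.35.

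**Step 3: how often the denominator is not clearly non-zero.**

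With z = d / SE, P(95% CI includes 0) = Φ(1.96 − z) − Φ(−1.96 − z), and P(estimate has the wrong sign) = Φ(−z). For example, at d = 0.2 and 70 per arm, z = 0.2 / 0.169 = 1.18, giving 0.78 and 0.12.

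| True difference d (assumed) | CI includes 0, 70/arm | CI includes 0, 63/arm | Wrong sign, 70/arm |
|---|---|---|---|
| 0 | 95% | 95% | 50% |
| 0.1 | 91% | 91% | 28% |
| 0.2 | 78% | 80% | 12% |
| 0.3 | 57% | 61% | 4% |
| 0.4 | 34% | 39% | 1% |
| 0.5 | 16% | 20% | 0.2% |

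**Step 4: what this does to the ratio.**

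Let C be the estimated incremental cost and D the estimated days avoided, with variances V_C and V_D and covariance V_CD. The 95% Fieller set is every R that satisfies

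R²(D² − 1.96²V_D) − 2R(CD − 1.96²V_CD) + (C² − 1.96²V_C) ≤ 0.

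The set is a bounded interval only if the coefficient of R² is positive, that is, if |D| > 1.96√V_D. This is the condition that the 95% CI for the day difference excludes zero. The column of CI probabilities in Step 3 is therefore also the chance that the Fieller set for the ratio is unbounded. Any finite interval printed in that case understates the uncertainty.

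**Step 5: the sign.**

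A saving of C with D days avoided gives −C/D. An extra cost of C with D days added gives C/(−D) = −C/D. The ratio is the same and the conclusion is opposite.

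**The case against.** Four arguments stand against the point.

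1. *The trouble is conditional.* The documents give no hospital-day effect or SD. If the true difference is near 0.5 SD, the denominator's interval includes zero only about 16% of the time at 70 per arm. This stands: a reader might infer that the interval is bound to be uninterpretable, and the documents do not support that.

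2. *The protocol names no percentile method.* How the interval is built, and how dominance is handled, could be set out in an analysis plan that is not shown. The first half is right, and the point does not rest on a percentile interval: Step 4 applies to any finite interval for the ratio. The second half goes only so far, because the protocol itself commits to a 95% interval for the ICER, and a plan that follows this wording inherits the problem.

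3. *Part of the remedy is already there.* Section 3.12 vi makes a cost comparison part of the primary analysis, performs the ICER afterwards, and plans an absolute difference with a 95% interval and extensive sensitivity analysis. Section 3.12 iv compares the health system outcomes between groups. A reader might conclude that the economic result as a whole would be lost. That goes too far: cost, and plausibly service use, would still be reported apart from the ratio. None of this repairs the interval for the ratio itself.

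4. *Seventy per arm may understate the numbers for service use.* Section 3.7 expects about 50% of 400, which is 200 or 100 per arm, and section 4.1 offers families who decline the questionnaires consent to use of administrative data. The gain from the latter is not stated. At 100 per arm the threshold falls only to 1.96 × √(2/100) = 0.28 SD, and at d = 0.2 the denominator's interval still includes zero about 71% of the time.

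**Conclusion.** The point holds in conditional form. The protocol fixes a 95% confidence interval for a ratio whose denominator was not considered in sizing the trial and whose numerator it expects may take either sign. Unless the true difference in hospital days exceeds about 0.33 SD (70 per arm) or 0.35 SD (63 per arm), the denominator's interval is more likely than not to include zero. The ratio then has no bounded 95% Fieller interval, and negative values are ambiguous.

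These figures rest on a normal approximation and on assumed standardised differences. Hospital days are likely to be skewed, which the approximation ignores. No figure in dollars per day is offered, because the documents give no costs, SDs or correlation from which to derive one.

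The three co-primary outcomes are not affected. The change should be made, because this ratio is how the protocol says cost-effectiveness will be expressed.

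**What to change.** Amend section 3.4 (Health System Outcomes) and section 3.12 vi together, so that the ICER's 95% confidence interval is no longer the measure of uncertainty. In its place report:

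- incremental cost and incremental hospital days, each with its own 95% confidence interval, building on the cost comparison and absolute difference already in 3.12 vi;
- the joint draws of the two on the cost-effectiveness plane;
- incremental net benefit, or an acceptability curve, over a stated range of values per hospital day avoided.

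Give an ICER with an interval only when the day difference is clearly non-zero and neither arm dominates; otherwise state which arm dominates or that the ratio is not estimable. Apply the same rule to the emergency-visit ICER and to both perspectives.

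The cost is slightly more reporting. The same sensitivity-analysis or bootstrap draws serve, and no new data or patients are needed.
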